In the current project, we aim to test the effectiveness of the ‘keeping phase’ of the SEd toolkit more extensively and systematically using a randomized controlled trial (RCT) at an institute for intermediate vocational education and a university of applied sciences in the Netherlands. This RCT will be the first to assess the effect of the individualized SEd intervention on ‘remaining at school’ (primary outcome), next to indicators of study success and student satisfaction. These outcomes were chosen as remaining at school, and increasing study success and student satisfaction are the goals of SEd, and increasing the capacity of people to be successful and satisfied in the living, working, learning, and social environments of their choice is also the mission of PRA of which SEd is derived. Student satisfaction is strongly related to study success [22], and to involuntary dropout (i.e. students who were dismissed for failure to meet minimum academic standards) [23]. Furthermore, student satisfaction also influences students’ decision to continue with or drop out of school [24] even in students who were in good academic standing, but choose to dropout [23]. Examining whether the SEd intervention positively influences student satisfaction is therefore of high relevance. We are aware of only three RCTs on the effectiveness of SEd [25–27]. These studies differ from our RCT on several aspects: the type and contents of the intervention, the target group and the outcomes. Collins and colleagues [25] and Mowbray and colleagues [27] studied the effect of two *group* SEd interventions: a classroom intervention and a group model intervention that were more aimed at preparing for going to school, than at remaining at school. Collins and colleagues [25] found that students in the classroom model showed higher levels of empowerment and school self-efficacy than students in the control condition. Additionally, they found that the level of satisfaction with the program of the students receiving the group model intervention was significantly higher than of the students in the control condition. Mowbray and colleagues [27] only performed within-group analyses, so no conclusions can be drawn about the differences on the outcome variables between the experimental condition and the control condition. An RCT by Ellison and colleagues [26] was performed among *veterans* with post-traumatic stress disorder and showed that veterans in the SEd condition spent a greater amount of time on educational activities than the veterans in the control condition. In addition, several *pilot* studies on SEd have been performed (see for an overview of studies published between 1989 and 2009: [28], and for an overview of studies published between 2010 and 2020: Büttner S, Hofstra J, Farkas M, van der Velde J, Korevaar EL: Supported Education for students with mental health conditions: a systematic review of effectiveness studies from 2009-2020, submitted), showing positive effects on for instance educational status and level of employment [29, 30], study enrollment [31, 32], and Grade Point Average [29, 32]. However, the lack of a randomized controlled group in these studies limits the ability to draw strong conclusions. Although existing studies indicate that SEd may be an effective tool to support students with mental health problems, the outcome variables that were studied were very diverse and it remains to be determined whether SEd increases the chance that students remain at school, which is the ultimate goal of the keeping phase of SEd. If SEd is to become a viable alternative and widespread intervention and if mental health and education policies are to emphasize educational attainment, more effectiveness research on SEd models is critically needed [28, 33]. Therefore, in the current study we aim to examine the effect of SEd on remaining at school, next to study success and student satisfaction, using a mixed-methods design. The effect of SEd will be compared with the effect of an active control condition in which students will receive support as usual plus advice from a trained educational staff member on potential supportive resources. We chose for an active control condition to make sure that potential differences in effects of the intervention and control group cannot be attributed to general effects of receiving support, like getting attention from professionals, or being part of a group. Moreover, we thought it to be unethical to not support students who indicate that they are in a current need for support with their school functioning because of their mental health problems.

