### Research aims

This study involves an effect evaluation (RCT) and a process evaluation (qualitative research) of SEd. The first question that will be addressed is:
A)What is the effect of the SEd intervention on remaining at school (primary outcome), study success and student satisfaction (secondary outcomes) of students with mental health problems who follow post-secondary education, as compared to students with mental health problems who receive support as usual plus advice from a trained educational staff member on potential supportive resources?

We plan to test the following hypotheses:
More students who receive the SEd intervention will remain at school or graduate as compared to students who receive support as usual plus advice on potential supportive resources.Students who receive the SEd intervention will be more successful at school, operationalized as a higher GPA and a higher number of credits and courses completed, than students who receive support as usual plus advice on potential supportive resources.Students who receive the SEd intervention will experience a higher level of satisfaction at school than students who receive support as usual plus advice on potential supportive resources.

The second research question that will be addressed is:
B)What are the essential components of the SEd intervention according to students and SEd specialists?

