#### Secondary study outcomes

Secondary study outcomes are study success and student satisfaction.

*Study success* will be measured with the following indicators: grade point average per semester; number of credits completed per semester; and number of courses completed.

*Student satisfaction* will be determined by the school subscale of the Multidimensional students’ life satisfaction scale [48, 49], which consists of eight items measuring the overall satisfaction of the student at school. Students indicate on a 4-point scale, ranging from 1 (Rarely) to 4 (Always) to what extent the statements, such as ‘I like the activities at school’ and ‘I learn a lot at school’ are applicable to them.

Furthermore, the following measures will be included in order to examine whether the scores of the students in the two conditions differ on these aspects which could account for any possible effects:

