### Proposed analyses

Analyses will be performed according to the intention-to-treat principle and we will control for any variation in observable characteristics between conditions that remained after the minimization procedure that was used to randomize the students into the conditions. Missing values in the questionnaires will be prevented as the questionnaires are administered through an online secure software program (Enalyzer) in which answering to all items is obligated. The main outcome measure (remaining at school) will be insensitive for missing values as this data can be retrieved from the administration offices of the educational institutes. In case of missing data (for example, when a student does not fill in the second or third questionnaire), intention-to-treat analyses will be performed to account for incomplete outcome data [55]. In addition, it will be examined whether the rates of incomplete data differ between the control and experimental condition. To detect any outliers, the median absolute deviation method will be used [56]. Unrealistic outliers (due to e.g. data entry mistake) will be removed. In case of outliers with a realistic value, we will perform the analyses both with and without the outliers and we will report both results.

Descriptive statistics (e.g. frequencies, means and standard deviations) will be provided for all variables. Conventional statistical tests (e.g. regression, chi-square and ANOVA) will be used to address the research questions in accordance with how the data align with the assumptions of these tests (e.g. normality, homogeneity). In case the data are not normally distributed, the non-parametric equivalents will be used (e.g. the Friedman-test, the Mann-Whitney-test and the Wilcoxon signed-rank test).

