With respect to the primary outcome, remaining at school, we will compare the number of students who remained in education or graduated in the experimental and the control condition at T2. Logistic regression models will be conducted to test the differences between the experimental and control condition. In addition, the differences in scores on the secondary outcomes, study success and student satisfaction, will be examined for T0 to T2 using chi squares or repeated measures of variance with the ANOVA test using 95% confidence levels, respectively. Furthermore, the differences between the two conditions on number and duration of contacts with the SEd specialist, the trained staff member or students service provider; the number of study skills where the students need support with and the number of resources needed or used when studying, student general self-efficacy levels and the working alliance with the professional, will be calculated using the ANOVA test with 95% confidence levels. Moreover, to test whether outcomes are similar for students from both educational institutions, sensitivity analyses will be performed excluding students from the institute for intermediate vocational education.

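### Chi-square is assigned to the numeric study-success outcomes, and no between-arm contrast is named for student satisfaction or its non-normal fallback

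*Protocol article*

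**What the plan says.** All references are to the protocol article.

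- **Hypotheses (Research aims).** Study success is "operationalized as a higher GPA and a higher number of credits and courses completed" in the Supported Education (SEd) arm than in the control arm. For satisfaction, SEd students "will experience a higher level of satisfaction at school than students who receive support as usual" plus advice. Both are comparisons between arms.
- **Outcomes (Secondary study outcomes).** Study success is measured by "grade point average per semester; number of credits completed per semester; and number of courses completed". Satisfaction is an eight-item subscale with 4-point items. Table 1 schedules both at baseline, 6 and 12 months.
- **Tests (Proposed analyses).** Score differences on "study success and student satisfaction, will be examined for T0 to T2 using chi squares or repeated measures of variance with the ANOVA test", at 95% confidence levels, and the sentence closes with *respectively*.
- **Fallback (same section).** If data are not normal, "the non-parametric equivalents will be used (e.g. the Friedman-test, the Mann-Whitney-test and the Wilcoxon signed-rank test").
- **Covariates (same section).** The analyses are to control for differences between conditions that remain after minimisation. Study procedures lists the minimisation factors, and the number of credits completed is one of them.
- **The protocol's own standard (Background).** It says that the authors of an earlier trial of group SEd interventions "only performed within-group analyses, so no conclusions can be drawn about the differences on the outcome variables" between its conditions.

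**The concern.** The sentence on secondary outcomes names study success first and satisfaction second, then chi-square first and repeated-measures ANOVA second, and closes with *respectively*. Chi-square therefore falls to GPA, credits and courses. It is a test for categories, so it cannot be run on these outcomes until someone chooses cut-points, and the protocol gives none. That leaves a choice that could be made after the data are seen. It also discards information and has no place for the T0 value.

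For satisfaction the named method can do the job, but the sentence does not say which term tests hypothesis 3. In a repeated-measures ANOVA the time effect, the condition effect and the interaction answer different questions. If the data are not normal, the repeated-measures tests in the example list compare time points within students and have no arm term.

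Two of the three stated hypotheses rest on these sentences.

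**Working it through.** **1. Scale of outcome against test.**

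| Outcome | Scale in the protocol | Test assigned | Arm comparison? |
|---|---|---|---|
| GPA per semester | numeric | chi-square | only after an unstated categorisation |
| Credits per semester | count | chi-square | same |
| Courses completed | count | chi-square | same |
| Satisfaction | 8-item score at T0, T1, T2 | repeated-measures ANOVA | yes, through condition-by-time; term not named |

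**2. Baseline and covariates.** A chi-square test of arm by category at T2 has no covariate term. It cannot use the T0 value, although the sentence speaks of T0 to T2, and it cannot carry out the promised control for residual imbalance. As written, the two instructions in Proposed analyses cannot both be followed for study success.

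**3. The fallback list.**

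| Test | Compares |
|---|---|
| Friedman | time points within students |
| Mann-Whitney | arms |
| Wilcoxon signed-rank | two time points within students |

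Two of the three do not contain the contrast that hypotheses 2 and 3 need.

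**4. Cost of categorising.** No figure in the protocol depends on this point, so the following is an illustration.

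Inputs: 51 evaluable students per arm and a standardised difference of 0.5 (both from Sample size calculation, where they refer to the primary outcome). Assumptions: two-sided 5% test, normal data, median split.

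The 51 itself is reproduced by a one-sided two-sample t-test at 80% power (50.15, rounded up). A two-sided test needs 64 (63.77, rounded up). That is why the t-test below stays under 80%; it is a separate matter.

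*Comparison of means:*
- z = 0.5 / √(2/51) = 0.5 / 0.1980 = 2.525
- power = Φ(2.525 − 1.960) = Φ(0.565) = 0.71

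*Chi-square after a median split:*
- The cut lies midway between the arm means, 0.25 SD from each, so the proportions above it are Φ(0.25) = 0.599 and Φ(−0.25) = 0.401; difference 0.197
- SE under no difference = √(2 × 0.25 / 51) = 0.0990
- SE under the alternative = √(2 × 0.599 × 0.401 / 51) = 0.0971
- power = Φ((0.1974 − 1.96 × 0.0990) / 0.0971) = Φ(0.03) = 0.51

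A simulation agrees (2,000 runs per setting, three time points, assumed within-person correlation 0.6, a true 0.5 SD difference at T2, shared rise from T0 to T2 of 0 or 0.3 SD):

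| Test at T2 | No shared rise | Shared rise 0.3 SD |
|---|---|---|
| t-test | 69.5% | 72.0% |
| Mann-Whitney | 67.2% | 70.2% |
| Chi-square, median split | 50.0% | 52.1% |

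The loss is about 20 percentage points against the t-test. Mann-Whitney loses only about 2.

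**The case against.** **Loose drafting.** The sentence joins its two methods with *or* and then adds *respectively*. The same section says that regression, chi-square or ANOVA will be used according to how the data meet each test's assumptions. On that rule GPA and credits could go to regression or ANOVA. This softens the point but does not repair it: the specific sentence still assigns chi-square, and the reader is left with two instructions that disagree.

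**The named tests are not all unfit.** A reader might infer that none of them can answer the between-arm hypotheses. The document does not support that. Repeated-measures ANOVA can test hypothesis 3 through condition-by-time, Mann-Whitney compares arms, and chi-square on categorised data also compares arms, only inefficiently.

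**No within-arm decision rule is stated.** A reader might also infer that, with skewed data, hypothesis 3 would be judged by whether each arm improved, and might attach a false-positive rate to that rule. The fallback is an open list of examples, assigns no test to satisfaction, and nowhere says that the arms will be tested separately. The hypotheses are worded between arms, and the Background shows that the authors know the limits of within-group analysis. What stands is narrower: the list includes tests with no arm term and does not exclude them for these hypotheses.

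**The size is conditional.** The protocol mentions no median split, and the power figures assume normal data. They do not carry over directly to counts of credits or courses.

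**Detail left to an analysis plan.** The exact fallback model may properly sit there. A test that does not fit its outcome, stated in the protocol, is a different matter.

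**Conclusion.** The test stated for study success does not fit the outcome. That follows from the text alone: numeric indicators, a hypothesis about higher amounts, no categories, and a test that can use neither the T0 value nor covariates. If the mismatch were resolved by a median split, power for a 0.5 SD difference with 51 per arm would be about 50% instead of about 70%; other cut-points would give other figures.

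For satisfaction the method is usable. The defect is that the contrast is unnamed and that the example fallback does not secure an arm comparison. The document does not show that within-arm tests would decide the hypothesis, so no error rate for such a rule belongs to this finding.

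Severity: should be fixed. Only secondary outcomes are affected. The primary outcome has its own between-arm analysis, logistic regression at T2, which this point leaves untouched.

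**What to change.** In Proposed analyses:

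1. **Study success.** Delete chi-square. Use a between-arm regression at T2 with condition, institute and the T0 value where available. For courses, use a count or proportion model if needed. The eligibility criteria set no minimum time in the programme, so new students may have no T0 GPA; add a rule for them.
2. **Satisfaction.** Name the term that tests hypothesis 3: condition-by-time if T0 is one of the repeated measurements, or the condition effect if T0 enters as a covariate.
3. **Non-normality.** State that the same between-arm contrast is kept, with robust or bootstrap confidence intervals, or with Mann-Whitney. The first two keep the covariates; a plain Mann-Whitney test does not. State that Friedman and signed-rank tests are not used for hypotheses 2 and 3.

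The cost is rewording a few sentences plus the rule for missing T0 GPA. Table 1 already schedules the outcomes at T0, 6 and 12 months, so no new measurement is needed.

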### Sample size calculation

As mentioned before, this is the first RCT on the effect of our SEd intervention on remaining at school, our main outcome measure. Therefore, the effect size of our intervention on remaining at school is unknown. In such cases, it is a common convention to set the effect size at 0.5 [35], because a lower effect size would not be considered as clinically relevant [36, 37]. Therefore, we aim to demonstrate an effect size of 0.5 on the primary outcome measure remaining at school with a power of 80% and an alpha < 0.05.

Hence, for each condition 51 students are needed (total 102). Given an expected drop-out percentage of 25% from the study, 140 students (2 × 70) need to be included in the study. This is a feasible number, considering that 20–45% of students worldwide experience mental health problems [1, 38, 39].

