### Study procedures

We adhere to the SPIRIT 2013 guidelines [40], the checklist is provided in the Additional file 2.

Students who heard about the study through one of the recruitment strategies and are interested in participation, contact the research team by e-mail. A data coordinator will check the inclusion criteria and will then send a link to an online questionnaire which starts with information about the study and the question to fill out an informed consent form. In the informed consent (see Additional file 3), students state that they have been informed about the study and that they participate voluntarily. In addition, they give permission to collect grades and course credits from the school’s administration for the next five years, so we are able to follow the study success of the students after the current project has finished. They also give permission that in case they drop-out of the study, school progress keeps being monitored. Students have the right to withdraw this permission at any moment in time.

After signing the informed consent, the students fill out the baseline-questionnaire. Then, students will receive a student ID number and will be randomized, for both educational institutes separately, by the data coordinator in either the experimental condition (Supported Education-coaching; half of the group of students) or the control condition (support as usual plus advice on potential resources; half of the group of students), using the minimization approach [41] which aims to minimize imbalance between the conditions on specific factors, in our case on gender, age, ethnicity, study year, level of study, the number of credits completed, and level of psychological distress. The condition to which the student is allocated depends on the characteristics of the students that were already enrolled. Students will receive compensation (a gift coupon of 12,50 euro each) for filling in the questionnaires at baseline, 6- and 12-month follow-up. Within this 12-month follow up, each student experiences a critical moment in the educational pipeline: either transitioning to the next year or graduating. In Table 1, the Spirit flow diagram of the study procedure is presented.

**Table 1 Tab1:** SPIRIT flow diagram of the study procedure showing enrolment, interventions, and assessments

	Pre-intervention	Post-intervention (within one month)	6 month follow-up	12 month follow-up
**TIMEPOINT**	**t**_**0**_		***t***_***1***_	***t***_***2***_

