**Student satisfaction**				
*The students’ life satisfaction questionnaire – school subscale*	X		X	X

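### Satisfaction is analysed with the pre-randomisation score as an outcome level and no term fixed as the test of hypothesis 3; adjusting T1 and T2 for T0 would be clearer and usually stronger

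*Protocol article*

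**What the plan says.** The Proposed analyses section says that differences on the secondary outcomes, study success and satisfaction in that order, "will be examined for T0 to T2 using chi squares or repeated measures of variance with the ANOVA test". The sentence closes with the word respectively, which pairs chi-square with study success and repeated-measures ANOVA with satisfaction. No model term is named.

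Hypothesis 3, under Research aims, reads "Students who receive the SEd intervention will experience a higher level of satisfaction at school" than students in the control condition. It gives no time point and does not say whether level or change is meant.

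Under Study procedures the order is: "After signing the informed consent, the students fill out the baseline-questionnaire. Then, students will receive a student ID number and will be randomized". The row "The students’ life satisfaction questionnaire – school subscale" in Table 1 is marked at t0, t1 (6 months) and t2 (12 months). Satisfaction at T0 is therefore a pre-randomisation measurement, and it is one of the three levels of the repeated outcome.

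The same section promises control for observable differences left after minimisation. It does not name baseline satisfaction, which is also not among the minimisation factors.

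**The concern.** Randomisation makes the expected T0 difference zero. A model that treats T0 as an outcome offers two terms for hypothesis 3, and each has a drawback.

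- **Condition main effect.** This is the term for a difference in level. Its null is equality of the mean over T0, T1 and T2. A wave that cannot respond is averaged in, and one third of any chance T0 difference enters the estimate.
- **Condition-by-time.** This uses T0 as a reference and does not average it in. With three waves it has 2 degrees of freedom and tests any difference in profile shape. It has no direction and does not in itself estimate a difference at T1 or T2.

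The two terms can give different answers from the same data, and the article does not say which one counts. T0 is already collected for every student and could be used as a covariate to sharpen the comparison.

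**Working it through.** **Inputs from the protocol.** 51 per condition, or 70 per condition recruited to allow for 25% drop-out; 140 × 0.75 = 105, about 52 per arm, so 51 is a fair figure for questionnaire completers. The effect size of 0.5 is stated for the primary outcome only ("we aim to demonstrate an effect size of 0.5 on the primary outcome measure remaining at school").

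**The plan's own figure.** No power is stated for satisfaction. The 51 per condition, "with a power of 80% and an alpha < 0.05", is reproduced by a one-sided t-test with d = 0.5 (50.15, rounded up to 51). A two-sided test needs 64. That is a separate matter; the figures below are two-sided at 5%.

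**Assumptions.** SD 1 at each wave, equal correlation ρ between waves, complete data, and condition differences of 0 / 0.5 / 0.5 SD at T0 / T1 / T2. With n = 51 per arm, √(2/51) = 0.198.

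**1. Condition main effect over T0-T2.** Mean difference (0 + 0.5 + 0.5)/3 = 0.333. SD of a three-wave mean = √((1 + 2ρ)/3).
- ρ = 0.5: noncentrality 0.333/(0.816 × 0.198) = 2.06, power 53%.
- ρ = 0.6: 0.333/(0.856 × 0.198) = 1.97, power 49.5%.

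**2. Condition-by-time, 2 and 200 df.** Sum of squared deviations of the profile = (1/3)² + 2 × (1/6)² = 0.167. λ = (51/2) × 0.167/(1 − ρ).
- ρ = 0.5: λ = 8.5, power 74%.
- ρ = 0.6: λ = 10.6, power 83%.

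**3. Mean of T1 and T2 adjusted for T0.** Residual variance = (1 + ρ)/2 − ρ².
- ρ = 0.5: 0.75 − 0.25 = 0.50, SD 0.707; 0.5/(0.707 × 0.198) = 3.57, power 94%.
- ρ = 0.6: 0.80 − 0.36 = 0.44, SD 0.663; 0.5/(0.663 × 0.198) = 3.81, power 97%.

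**Range over ρ (0 / 0.5 / 0.5, n = 51)**

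| ρ | Main effect | Condition-by-time | T2 adjusted for T0 | T1/T2 mean adjusted for T0 |
|---|---|---|---|---|
| 0.3 | 63% | 58% | 75% | 92% |
| 0.5 | 53% | 74% | 82% | 94% |
| 0.6 | 49.5% | 83% | 88% | 97% |
| 0.7 | 46% | 93% | 94% | 99% |
| 0.8 | 43% | 99% | 99% | 99.8% |

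With 70 per arm and ρ = 0.5 the row is 67%, 87%, 92%, 99%.

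**Other time profiles (ρ = 0.6, n = 51, same formulas)**

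| Profile | Main effect | Condition-by-time | T2 adjusted | T1/T2 mean adjusted |
|---|---|---|---|---|
| 0 / 0.25 / 0.5 (builds up) | 31% | 71% | 88% | 81% |
| 0 / 0.5 / 0.25 (fades) | 31% | 71% | 35% | 81% |
| 0 / 0 / 0.5 (T2 only) | 16% | 83% | 88% | 47% |

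For the last row, the adjusted mean has noncentrality 0.25/(0.663 × 0.198) = 1.90. The profile's sum of squares is again 0.167, so λ = 10.6.

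**The case against.** The strongest reply is that the plan never says it tests the main effect. Examining differences from T0 to T2 can be read as a difference in change, which is the condition-by-time term and the usual test in a pre-post repeated-measures ANOVA. On that reading T0 is not averaged in. Against T2 adjusted for T0, the loss for a constant effect is then only 9 points at ρ = 0.5, 4 at 0.6 and 1 at 0.7.

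This stands. A reader might infer that hypothesis 3 will be judged at about 50% power; the documents do not support that, because no term is named. Nor is the interaction always weaker than a baseline-adjusted test: it beats T2 alone when the effect fades, and beats the T1/T2 mean when the effect appears only at T2.

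A second reply is that naming the term belongs in a statistical analysis plan. Silence on the term alone would not be a finding. But the model itself is stated, and it makes T0 an outcome. That choice can be assessed, and a better use of the same data is available.

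A third reply is that the planned control for residual imbalance covers a chance T0 difference. It may in part, but it depends on imbalance being seen and does not name baseline satisfaction.

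A reader might also extend the point to every measure compared by plain ANOVA. The article does not say that T0 values will be ignored there, and it calls the skills and resources checklists descriptive, so little rests on them.

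**Conclusion.** The point holds as one of efficiency and clarity. The stated analysis uses a pre-randomisation score as an outcome level and leaves open which term answers hypothesis 3. Under the main effect, a constant effect is cut to two thirds and power is about 50-53% at ρ = 0.5-0.6 with 51 per arm. Under condition-by-time, power is 74% against 94% (ρ = 0.5) or 83% against 97% (ρ = 0.6) for the adjusted T1/T2 mean. At ρ = 0.7 the gap is 6 points, and at 0.8 about 1.

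All of these figures assume 0.5 SD for satisfaction, equal correlations, a constant effect and complete data. The protocol gives none of these for this secondary outcome. There is no bias or type I error problem, and the primary outcome is unaffected.

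**What to change.** Replace the T0-to-T2 repeated-measures ANOVA for satisfaction by a model with T1 and T2 as outcomes, T0 as covariate, and condition, time and condition-by-time as terms. Name one baseline-adjusted condition contrast, with its 95% CI, as the test of hypothesis 3. There are two reasonable choices:

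- **The T1/T2 average.** It holds up when the effect builds or partly fades, but is weak if the effect appears only at T2.
- **T2 alone**, if 12 months is the time of interest, accepting lower power if the effect fades.

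The choice should be made before outcome data are seen. Use T0 as covariate for self-efficacy in the same way. For the skills and resources counts this is optional.

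The cost is one or two sentences of analysis wording, with no extra students, visits or data.

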**Methods/design:**

The design combines quantitative research (Randomized Controlled Trial; RCT) with qualitative research (monitoring, interviews, focus groups). One hundred students with mental health problems recruited from the two educational institutes will be randomly allocated to either the intervention or control condition. The students in the intervention condition receive the Supported Education intervention given by a Supported Education specialist, the students in the active control condition receive support as usual plus advice from a trained staff member on potential supportive resources regarding studying with mental health problems. The primary outcome ‘remaining at school’, and the secondary outcome ‘study success’ will be determined using data from the school’s administration. The secondary outcome ‘student satisfaction’ and other variables that will be studied in a more exploratory way, such as self-efficacy and study skills, will be determined through online questionnaires at baseline, at 6 and at 12 months follow-up. Focus groups and interviews with the students and Supported Education specialists will be carried out to complement the trial.

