**Other measures**				
*List with study skills*	X		X	X
*List with resources*	X		X	X
*The General Self-Efficacy scale*	X		X	X
*The Working Alliance Inventory*			X	X

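### Self-efficacy, study skills and resources are compared by an ANOVA with no planned baseline term, although each has a pre-randomisation score that would make the comparison more precise

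*Protocol article*

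**What the plan says.** One sentence in Proposed analyses lists five kinds of variable on which the conditions will be compared: contacts with the professional, "the number of study skills where the students need support with and the number of resources needed or used when studying", and finally "student general self-efficacy levels and the working alliance with the professional, will be calculated using the ANOVA test with 95% confidence levels". It gives no time point, covariate or time factor. The sentence before it, on the secondary outcomes, is more specific: those differences "will be examined for T0 to T2 using chi squares or repeated measures of variance with the ANOVA test".

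Three of the five variables have a baseline value. Table 1 marks the study-skills list, "List with resources" and "The General Self-Efficacy scale" at t0, t1 and t2. The abstract agrees for two of them: variables "such as self-efficacy and study skills, will be determined through online questionnaires at baseline, at 6 and at 12 months follow-up". The Working Alliance Inventory is marked at t1 and t2 only, and contacts cannot precede the intervention.

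The T0 scores precede allocation. Study procedures says: "After signing the informed consent, the students fill out the baseline-questionnaire. Then, students will receive a student ID number and will be randomized". The minimisation factors listed there are gender, age, ethnicity, study year, level of study, credits completed and psychological distress. None of the three measures is among them.

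The only adjustment rule is general: "we will control for any variation in observable characteristics between conditions that remained after the minimization procedure".

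**The concern.** The sentence applies one test to variables with a baseline and variables without one. A test shared with contacts and working alliance cannot be one that uses T0, and the authors name repeated measurement in the preceding sentence, where they intend it. The natural reading is therefore a between-arm ANOVA of follow-up scores.

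On that reading, stable differences between students stay in the error term although a measurement taken before randomisation could remove part of them. Intervals are then wider than the data require. The general adjustment rule does not secure the gain, because it depends on an observed difference between the arms. It also leaves the choice of model to be made after the baseline data are seen.

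What is at stake is precision and prespecification. The section on secondary outcomes says these measures serve to see whether the conditions differ on aspects that might explain an effect, so an imprecise comparison weakens that explanation.

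**Working it through.** The plan gives no sample size, power or effect size for these comparisons. Its calculation of 51 per condition is for the primary outcome, so there is no stated figure to reproduce here.

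**Inputs**
- Students: 140 to be included with 25% expected drop-out (Sample size calculation), giving 140 × 0.75 = 105, or 52.5 per arm.
- Test: two-sided 5%, matching a 95% confidence level.
- Correlation r between the T0 and follow-up scores: not in the document. Assumed 0.3 to 0.7.
- True difference: not in the document. Assumed 0.4 SD.

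**Formulas** (in SD units of the follow-up score)
- Unadjusted standard error: √(2/n) = √(2/52.5) = 0.195.
- With the T0 score as covariate, error variance is multiplied by 1 − r², so the standard error is 0.195 × √(1 − r²).
- Equivalent sample multiplier: 1/(1 − r²).
- Power: noncentral t with 103 degrees of freedom and noncentrality 0.4 divided by the standard error. The one further degree of freedom used by the covariate makes no visible difference.

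| r | Variance cut | Standard error | Sample multiplier | Power at 0.4 SD |
|---|---|---|---|---|
| no adjustment | – | 0.195 | 1.00 | 52.8% |
| 0.3 | 9% | 0.186 | 1.10 | 56.7% |
| 0.4 | 16% | 0.179 | 1.19 | 60.1% |
| 0.5 | 25% | 0.169 | 1.33 | 65.0% |
| 0.6 | 36% | 0.156 | 1.56 | 71.8% |
| 0.7 | 49% | 0.139 | 1.96 | 81.1% |

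Interval width scales with √(1 − r²): 0.954 at r = 0.3 and 0.714 at r = 0.7, so intervals are 5% to 29% narrower.

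**Chance imbalance at T0.** Under simple randomisation the T0 difference between arms also has standard error 0.195 SD. A gap above 0.2 SD in either direction has probability 2 × [1 − Φ(0.2/0.195)], about 31%. Unadjusted, such a gap shifts the follow-up difference by r times its size: 0.1 SD at r = 0.5.

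**Change score as an alternative.** Its variance factor is 2(1 − r), which is below 1 only when r exceeds 0.5. ANCOVA's factor, 1 − r², never exceeds 1. A simple change from baseline is therefore not a safe substitute.

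**The case against.** **The wording does not exclude T0.** The sentence gives no time point and does not call the ANOVA one-way. The sentence before it uses the same term for a repeated-measures analysis, and the listed non-parametric alternatives include within-subject tests. This stands in part: a time factor is not strictly ruled out. The between-arm reading is still the more natural one, and the ambiguity is itself a reason to reword.

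**The plan already adjusts.** A reader might infer that T0 is simply discarded and that chance baseline differences pass uncorrected into the arm difference. The documents do not support that. The general rule is not limited to minimisation factors and could bring in a T0 score on which the arms differ. What it lacks is a commitment to adjust when they do not.

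**The measures are exploratory.** The abstract says so, the Measurements section calls both checklists descriptive, and none of the three hypotheses concerns them. This stands and sets the priority. It does not remove the point, because the plan still specifies a between-arm comparison with 95% confidence for them.

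**Covariates belong in the analysis plan.** An article need not list them, and it mentions regression among its example methods. But here it names a test for a mixed list of variables, and that test suits only part of the list.

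**The correlation may be low.** Two of the three measures are self-constructed checklist counts with no stability reported, and the intervention works on skills and supports directly. This is fair, and is why the range starts at 0.3, where the gain is small.

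**Conclusion.** The point holds as one of precision and prespecification. Three exploratory measures have a T0 score taken before randomisation, and the plan does not commit to using it. Adjustment would cut error variance by 9% to 49% for an assumed r of 0.3 to 0.7. At an assumed difference of 0.4 SD with 105 completers, power would go from 53% to between 57% and 81%. Both r and the difference are assumptions; a lower r gives a smaller gain.

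A reader might go further and infer that the planned comparison is biased or invalid. It is not: an unadjusted comparison of randomised arms is valid, only less precise than it could be. The primary outcome and the secondary outcomes are analysed by other methods and are unaffected. Low priority.

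**What to change.** Split the sentence in Proposed analyses in two.

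- For self-efficacy, number of study skills and number of resources, prespecify ANCOVA: the follow-up score regressed on condition, the student's own T0 score and institute, whether or not the arms differ at T0. Institute belongs in the model because randomisation is done separately at each institute. State the follow-up time point to which the comparison refers.
- For contacts and working alliance, keep the unadjusted comparison, since neither has a T0 value.

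The cost is a change of wording and one degree of freedom for the T0 term (one more for institute). No new data are needed: the T0 scores come from the questionnaire that each student completes before randomisation.
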